## Abstract

**Background::**

Coronavirus disease 2019 (COVID-19) has caused serious damage to public health. COVID-19 has no vaccine or specific therapy; its mortality rate increases significantly once patients deteriorate. Furthermore, intensive monitoring of COVID-19 is limited by insufficient medical resources and increased risks of exposure to medical staff. We therefore aim to build an early warning and rapid response system (EWRRS) to address these problems.

**Method::**

The research is designed as a prospective cohort study, to verify a dynamic and interactive evaluation system; it includes patient self-reporting, active monitoring, early alarming and treatment recommendations. Adult patients diagnosed with COVID-19 will be recruited from Sept 2020 to Aug 2021 at a tertiary contagious hospital. Patients with life expectancy <48 hours, pregnant or lactating, in immunosuppression states or end-stage diseases will be excluded. The intervention is implementation of EWRRS to detect early signs of clinical deterioration of COVID-19 patients, to provide timely and efficient treatment suggestions by the system. EWRRS can determine the classification and interactive evaluation of patient information; the determination is based on the application of 3 different scenario modules, separately driven by patients, nurses, and physicians. The primary outcome is change in disease severity category after treatment. Secondary outcomes include the proportion of patients with different disease severity types; critical deterioration events; patients who had unplanned transfers to an intensive care unit (ICU) and required critical care interventions; intervals from warning to implementation of clinical interventions; hospital mortality; length of ICU and hospital stay; workload of medical staff and risks of exposure to COVID-19.

**Discussion::**

Our hypothesis is that EWRRS provides an example of an early identification, warning, and response system for COVID-19. In addition, EWRRS can potentially be extended to use as a grading metric for general critically ill patients in an ICU setting.

EWRRS is equipped with a complete data processing and evaluation system; it evaluates cut-off values for a variety of clinical parameters. An alarm module setting, applied to coronavirus pneumonia clinical signs/symptoms and clinical severity classifications, will warn when test measures are in excess of cut-off values, predicting when patient condition is becoming more severe. The alarm includes 2 levels, a lower level of warning and higher level of alarming. For instance, critical warning starts when heart rate and blood pressure fluctuate more than 20% from baseline. The lower warning level means oxygen saturation from pulse oximetry (SpO_2_) is more than 2% lower than 93%. If SpO_2_ further decreases, even with supplemental oxygen, it implies that the patient may have a severe course of the disease. The higher level of alarming then will be triggered. As a result, treatment recommendations can be made by physicians and nurses according to patient risk classification and warning level, considering the individual hospital's situation and capacities. These recommendations may include increasing the frequency of monitoring, change of oxygen therapy, advancing respiratory therapy, or transfer of patients to ICU. EWRRS can determine the classification and interactive evaluation of patient information based on the application of 3 different scenario modules—patient, nurses, and physician (Fig. 1): *Patient-driven data evaluation module.* Once admitted, each patient will be requested to log into this system via a predesigned smartphone app. Next, the system will prompt patients to enter their demographic information; it then will guide the self-evaluation and documentation of signs and symptoms under physician order. Subsequently, physicians will provide initial assessment, clinical classification and offer preliminary treatment recommendation according to patients’ current medical conditions. For mild/moderate cases, at least 2 daily self-reports of vital signs are required. The system will offer professional feedback, including suggestions on treatment and recovery to patients. *Nursing-driven data evaluation modul*e. The system will automatically load patient self-reported information, which becomes part of medical record, into this module. If there is any identified abnormal data from vital signs and lab tests, or overdue self-reporting, the system will trigger a warning for nursing to intervene. This could include close observation, more frequent monitoring, dietary management, and/or psychological support, etc. *Physician-driven data evaluation module*. Similar to the nursing data entry module, this module will include all of the key administrative clinical data relevant to that person, including demographics, nursing and physician progress notes, medical problems, medications, lab tests, and results from various diagnostic exams. The system will integrate all the information to identify patients with abnormal clinical presentation, project the disease progression, and provide a priority list of patients that require physician attention. According to different levels of notice (warning or alarming), physicians will decide if more frequent clinical monitoring, checks on blood gas, and alternative therapies are required. After these interventions, the system will reevaluate patients’ updated clinical data, reclassify patients, and adjust treatment plans if needed. This system will incorporate continuous feedback management: identify–feedback–intervene–evaluate–reidentify.

**Figure 1 F1:**
[figure not shown]
COVID-19 Early Identification, Warning, and Response System design flow chart: a continuous novel coronavirus pneumonia self-reporting cyclic feedback management system incorporating “identify-feedback-intervene-evaluate-reidentify.”

The COVID-19 EWRRS will facilitate early identification of patients that potentially may progress from mild or moderate to severe or critical illness. Moreover, the development of this system will also be helpful for identification and response for future epidemic disease crises and other public health emergency events.

## Methods

2

The protocol is reported according to the Standard Protocol Items: Recommendations for Interventional Trials Checklist.^[4]^ Our protocol has been registered on the Chinese Clinical Trial Registry (http://www.chictr.org.cn/index.aspx). The registration number was ChiCTR2000034680.

### Study design and aims

2.1

This is a stepped-wedge prospective mixed methods study exploring the feasibility of EWRRS, which is an interactive, multimodal screening program to support the early identification of potential patients who may progress from mild or moderate to severe or critical illness. The detailed study aims:

1.To improve the detection of early signs of clinical deterioration of COVID-19 patients and provide real-time data to the entire clinical team, thus improving team situation awareness of patient deterioration.2.To provide timely and efficient treatment suggestions for COVID-19 patients through the rapid response system, thereby promoting active management of deterioration, stabilizing patient conditions early and avoiding the progression of deterioration to a more serious degree.3.To reduce the workload and risks of occupational exposure of medical personnel during the epidemic through interactive, multimodular processes.4.To identify the COVID-19 progression patterns and characteristics through big data analysis, thus providing an example of EWRRS for future outbreaks of public health events. Moreover, such a system can potentially be extended for use as a grading EWRRS, to respond to deteriorating patients outside of an ICU setting.

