### Study population and setting

2.2

Patients are eligible for this study if they were diagnosed with COVID-19 according to the New Coronavirus Pneumonia Prevention and Control Program (7th edition), published by the National Health Commission of China.^[5]^ Inclusion criteria comprise the following: adult patients (18 years or older) with clear epidemiological history; fever and/or respiratory symptoms; normal or decreased white blood cell count and/or lymphocyte count; high degree of suspected imaging characteristics of novel coronavirus pneumonia; positive results of SARS-CoV-2 nucleic acid detection and serum-specific antibodies; ability to provide a signed informed consent form. Patients were excluded if known life expectancy was less than 48 hours, pregnant or lactating, diagnosed with end-stage diseases, or in immunosuppression states.

Clinical Classification of the COVID-19 patients is according to their disease severity upon admission: *Mild cases*: The clinical symptoms are mild and no pneumonia manifestations can be found in imaging. *Moderate cases*: Patients have symptoms such as fever and respiratory tract symptoms, etc. and pneumonia manifestations can be seen in imaging. *Severe cases*: Adults who meet any of the following criteria: respiratory rate ≥30 breaths /min; oxygen saturation ≤ 93% at a rest state; arterial partial pressure of oxygen (PaO_2_)/oxygen concentration (FiO_2_) ≤ 300 mm Hg; patients with > 50% lesion progression within 24 to 48 hours in lung imaging. *Critical cases*: Adults who meet any of the following criteria: occurrence of respiratory failure requiring mechanical ventilation; presence of shock; other organ failure that requires monitoring and treatment in the ICU.

*Hospital discharge criteria*: normal body temperature for more than 3 days; significantly improved respiratory symptoms, that is, no oxygen supplementation requirement, stable and normal vital signs for longer than 1 day; lung imaging showing obvious absorption and resolution of acute infiltrates; negative results of the nucleic acid test for SARS-CoV-2 two times consecutively, with at least a 1-day interval between tests.

Patient recruitment duration will last for a year, from September 2020 to August 2021. During the study period, patients diagnosed with COVID-19 will be directly admitted or transferred to Beijing Ditan Hospital, which is the government designated COVID-19 hospital.

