### EWRRS procedures

2.3

For recruited COVID-19 patients, the EWRRS will perform different levels of assessment for the patient alarm information, offering corresponding treatment recommendations (Fig. 2). The details in EWRRS procedures are as follows:

1.After admission, EWRRS performs an initial assessment of COVID-19 patient disease severity based on past medical history, clinical symptoms, vital signs, and other auxiliary examinations. It then classifies them into 3 clinical classifications: mild/moderate, severe, and critical cases. Similarly, during the subsequent treatment, EWRRS will reclassify patients according to the results of updated patient clinical data, if needed.2.For mild/moderate cases, EWRRS will provide “self-reported vital signs” twice to 3 times per day. During treatment, these cases may present mild abnormalities in vital signs or values in lab tests—chest tightness, shortness of breath, resting SpO_2_ less than 95% etc.; these will be regarded as “lower level warning” by the system. The system will then trigger a warning for nursing intervention, with treatment recommendations. These include “Increase frequency of SpO_2_ monitoring (every 4 hours),” “Oxygen therapy via nasal cannular,” and “Dietary and psychological support.”3.Cases where patient symptoms and lab values grow worse and meet the following standards: shortness of breath on exertion (e.g., getting out bed to bathroom); no symptom relief after 1-hour oxygen therapy via nasal cannular; SpO_2_≤95% with any oxygen therapy (nasal cannular or oxygen mask); respiratory rate ≥25/min with any oxygen therapy (nasal cannular or oxygen mask); ROX≤4.88 with any oxygen therapy (nasal cannular or oxygen mask). These worsening symptoms will be identified as “higher level alarming” by the system. Meanwhile, these patients will be reassessed as severe cases. The system will synchronously trigger a warning for physicians to intervene. As a result, these severe cases will receive more monitoring of SpO_2_, blood artery gas check and various intensive respiratory supports according to their PaO_2_/FiO_2_, a blood gas parameter that reflects oxygenation status.4.For severe cases—PaO_2_/FiO_2_ of ≥300 mm Hg; 200 to 300 mm Hg; and 150 to 200 mm Hg—treatment recommendations become “continue oxygen therapy,” “high-flow nasal cannula oxygen therapy, observe 2 hours,” and “noninvasive ventilation, observe 2 hours,” respectively. If these cases continue to deteriorate—altered mental status presented, severe cardiac arrhythmias, shock, airway obstruction, patients with PaO_2_/FiO_2_ <150 mmHg—they will be reevaluated as critical cases by the system; a treatment recommendation of “Call ICU consultation” would then be offered.

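### Section 2.1 calls the study stepped-wedge and the Abstract calls it a prospective cohort, while the procedures describe no comparator to support the effect wording in aims 1 to 3

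*Protocol article*

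**What the plan says.** The protocol article gives two design labels.

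- Section 2.1: "This is a stepped-wedge prospective mixed methods study exploring the feasibility of EWRRS".
- Abstract, Method: "The research is designed as a prospective cohort study, to verify a dynamic and interactive evaluation system".

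On setting, the Abstract says "Adult patients diagnosed with COVID-19 will be recruited from Sept 2020 to Aug 2021 at a tertiary contagious hospital", and section 2.2 says "patients diagnosed with COVID-19 will be directly admitted or transferred to Beijing Ditan Hospital, which is the government designated COVID-19 hospital".

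On exposure, the Abstract says "The intervention is implementation of EWRRS to detect early signs of clinical deterioration of COVID-19 patients". The Introduction, describing the patient-driven module, says "Once admitted, each patient will be requested to log into this system via a predesigned smartphone app". Section 2.3 opens its account of assessment after admission with "For recruited COVID-19 patients, the EWRRS will perform different levels of assessment for the patient alarm information".

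Section 2.1 lists four aims. Aim 1 includes improving detection of early deterioration, aim 2 includes avoiding progression to a more serious state, and aim 3 is to lower staff workload and occupational exposure. Aim 4 is to describe progression patterns. In section 2.4 the primary outcome is change in clinical classification. The secondary outcomes include unplanned ICU transfer, mortality, length of stay, staff workload and the interval from warning to intervention. Section 2.6 plans Pearson chi-square, Student t and Wilcoxon tests and does not name the groups to be compared.

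**The concern.** A stepped-wedge study gets its evidence from units that move from control to intervention at different calendar times, so that exposed and unexposed periods can be compared side by side. A prospective cohort study implies none of this. The two labels promise different kinds of evidence, and the procedures show only patients under EWRRS.

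Two things are at stake. First, the effect wording in aims 1 to 3 needs a contrast, and a plan followed as printed would credit EWRRS with change seen within exposed patients. COVID-19 patients change severity category under natural course and concurrent treatment whether or not a warning system is running. Secondly, a reader who sees stepped-wedge would credit the results with controlled evidence that the described procedures do not supply.

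**Working it through.** The article gives no sample size, number of clusters or number of steps, so there is no stated figure to reproduce. The check sets the text against what each label requires.

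1. **Do the labels agree?** No. The Abstract has a prospective cohort study and section 2.1 a stepped-wedge mixed methods study. Shortening a longer protocol can remove detail, but it does not explain two different designs.

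2. **Are the elements of a stepped wedge described?**
   - Clusters: none named. One recruiting hospital is given (Abstract; section 2.2), and no wards or other units are defined.
   - Steps or a switch order: none. There is one recruitment window, September 2020 to August 2021.
   - Control period: none. Section 2.3 applies EWRRS to recruited patients without distinction, and the Introduction has each patient asked to log in once admitted.
   - Other comparator (usual care, historical): none.
   - Plural sites in section 2.7.2: a general monitoring sentence that identifies no second recruiting site.

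3. **Can an effect be estimated from what is described?** Write the outcome of a patient in unit *j* at time *t* as

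   outcome = μ + β(t) + u(j) + θ·X(j,t),

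   where X = 1 under EWRRS and 0 otherwise, β(t) is calendar time and u(j) is the unit. If X = 1 for every patient described, only the sum μ + θ can be estimated, not θ itself. The primary outcome is then change within exposed patients, which mixes EWRRS with natural course and treatment. A stepped wedge separates θ from β(t) because X differs between units at the same *t*; nothing in the article describes such a difference.

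4. **Does the analysis section supply the contrast?** No. Section 2.6 names tests but no groups, and has no term for cluster or calendar time. If a stepped wedge were being run, these tests would not suit it: they would ignore correlation within clusters and would confound the switch with time.

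5. **Which aims are affected?** Improving detection, avoiding progression and reducing workload and exposure are comparative. Delivering real-time data and timely treatment suggestions (parts of aims 1 and 2) can be described in a single arm, as can feasibility and the progression patterns of aim 4.

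**The case against.** The strongest reply is that this is a journal article. Cluster definitions, switch dates and a control phase may stand in a full protocol that is not shown, and what an article commonly leaves out is no fault. Section 2.3 and the Introduction describe how EWRRS works, and the intervention phase of a genuine stepped wedge would read much the same. Section 2.6 plans comparisons, so a comparison phase is not excluded. Finally, section 2.1 gives the purpose as exploring feasibility, which needs no comparator.

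Much of this stands, and it limits the point.

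- A reader might infer that the study certainly has no unexposed patients. The article supports only that none is described.
- A reader might infer that one hospital rules out a stepped wedge. It does not, because wards could be the clusters. Nor does data capture by EWRRS rule it out, since data could be captured before alarms are activated.
- A reader might infer that every admitted patient receives EWRRS. Eligibility and consent apply, and section 2.3 speaks of recruited patients.
- A reader might infer that aims 1 to 3 fail altogether. Only their effect wording lacks support.

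The reply does not remove the two conflicting labels. Nor does it reconcile the stepped-wedge label with exposure text that makes no allowance for a control phase. The feasibility phrase does not cover the stated aims of avoiding progression and reducing workload and exposure.

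**Conclusion.** The concern holds in this form: the article prints two designs, describes the elements of a stepped wedge nowhere, and attaches effect wording to three of its four aims without a described contrast. As described, an EWRRS effect is not identifiable. That does not mean EWRRS has no effect, only that the described data could not tell it apart from natural course, concurrent treatment or calendar time.

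The size is structural and cannot be put as a bias or error rate, because the article gives no comparison from which to compute one. The conclusion rests on the printed labels and exposure text, not on missing step details. It would change if a fuller document defined clusters and a pre-EWRRS period, but the Abstract, Introduction and section 2.3 would then still need to be brought into line. The point should be settled because it decides what the study may conclude.

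**What to change.** State one design, in the same words, in the Abstract and section 2.1.

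**If there is no control phase:** delete stepped-wedge, call the study a single-arm prospective cohort, and remove the effect wording from aims 1 to 3. Limit the conclusions to:

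- feasibility: completion of self-reports, and the warning-to-intervention interval already listed in section 2.4;
- alarm performance: sensitivity, positive predictive value and lead time against the section 2.2 categories, using the alarm log recorded under section 2.5. The reference should be the clinical experts' classification (section 2.4), because under section 2.3 a higher-level alarm itself reclassifies the patient as severe, and the system would otherwise be validated against itself.

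This costs wording only, with no new data collection. The downside is a weaker claim. Alarms also prompt treatment, so the performance figures describe the system in use and should be reported as such.

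**If a stepped wedge is truly intended:** state the clusters, the switch schedule and the pre-EWRRS period, and reconcile the Introduction and section 2.3 with them. Replace the simple tests in section 2.6 with an analysis that has cluster and calendar-time terms. If these elements already exist in a full protocol, the cost is text and a revised analysis section. If they do not, this is a redesign needing an amendment, and should not be treated as a correction of wording.

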### Study population and setting

2.2

Patients are eligible for this study if they were diagnosed with COVID-19 according to the New Coronavirus Pneumonia Prevention and Control Program (7th edition), published by the National Health Commission of China.^[5]^ Inclusion criteria comprise the following: adult patients (18 years or older) with clear epidemiological history; fever and/or respiratory symptoms; normal or decreased white blood cell count and/or lymphocyte count; high degree of suspected imaging characteristics of novel coronavirus pneumonia; positive results of SARS-CoV-2 nucleic acid detection and serum-specific antibodies; ability to provide a signed informed consent form. Patients were excluded if known life expectancy was less than 48 hours, pregnant or lactating, diagnosed with end-stage diseases, or in immunosuppression states.

Clinical Classification of the COVID-19 patients is according to their disease severity upon admission: *Mild cases*: The clinical symptoms are mild and no pneumonia manifestations can be found in imaging. *Moderate cases*: Patients have symptoms such as fever and respiratory tract symptoms, etc. and pneumonia manifestations can be seen in imaging. *Severe cases*: Adults who meet any of the following criteria: respiratory rate ≥30 breaths /min; oxygen saturation ≤ 93% at a rest state; arterial partial pressure of oxygen (PaO_2_)/oxygen concentration (FiO_2_) ≤ 300 mm Hg; patients with > 50% lesion progression within 24 to 48 hours in lung imaging. *Critical cases*: Adults who meet any of the following criteria: occurrence of respiratory failure requiring mechanical ventilation; presence of shock; other organ failure that requires monitoring and treatment in the ICU.

*Hospital discharge criteria*: normal body temperature for more than 3 days; significantly improved respiratory symptoms, that is, no oxygen supplementation requirement, stable and normal vital signs for longer than 1 day; lung imaging showing obvious absorption and resolution of acute infiltrates; negative results of the nucleic acid test for SARS-CoV-2 two times consecutively, with at least a 1-day interval between tests.

Patient recruitment duration will last for a year, from September 2020 to August 2021. During the study period, patients diagnosed with COVID-19 will be directly admitted or transferred to Beijing Ditan Hospital, which is the government designated COVID-19 hospital.

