### Ethics and dissemination

2.8

Study patients or their authorized surrogates received sufficient explanation and time to sign the informed consent form before the trial. Researchers ensured that the study was conducted in accordance with the principles of the Declaration of Helsinki and the clinical trial quality management regulations in China. The study protocol has been approved by the Ethics Committee of Beijing Tsinghua Changgung Hospital (20262-0-01).

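### The inclusion list requires pneumonia on imaging, so no patient who is mild on admission is eligible, although the study aims to detect progression from mild disease

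*Protocol article*

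**What the plan says.** Section 2.2 (Study population and setting) opens by making patients eligible if they have a COVID-19 diagnosis under a national programme. The study's own list follows: "Inclusion criteria comprise the following: adult patients (18 years or older) with clear epidemiological history", then symptoms, blood counts, the imaging and laboratory items ("high degree of suspected imaging characteristics of novel coronavirus pneumonia; positive results of SARS-CoV-2 nucleic acid detection and serum-specific antibodies") and the consent item. Semicolons separate the items, and nothing says that a subset is enough.

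The next paragraph sets out four severity classes and when they are assigned: "Clinical Classification of the COVID-19 patients is according to their disease severity upon admission". The mild class reads: "The clinical symptoms are mild and no pneumonia manifestations can be found in imaging". The moderate class requires visible pneumonia.

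Section 2.3 (EWRRS procedures) reduces four classes to three: "It then classifies them into 3 clinical classifications: mild/moderate, severe, and critical cases". The mild and moderate cases are the ones who self-report vital signs.

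The end of the Introduction and Section 2.1 both give the purpose as early identification of patients who may worsen from mild or moderate to severe or critical illness. The primary outcome in Section 2.4 is change in clinical classification, and one secondary outcome is the proportion of patients in each severity type.

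**The concern.** An inclusion criterion and a class definition in the same section exclude each other. If recruiters follow the list, every patient who is mild on admission is turned away, and those patients are part of the population that the system was built for. The results would then describe moderate-to-severe progression while the stated purpose also covers mild disease. If recruiters do not follow the list, mild patients enter against the written criteria. Either way, a reader could not tell from the protocol which population the change in classification refers to.

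**Working it through.** The point rests on no figure in the article, so the check sets the passages side by side.

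**Step 1. Are the inclusion items cumulative?** The list never says that all items are required, so this has to be read from the drafting of Section 2.2.
- Age and consent sit in the same list and are plainly mandatory.
- Where the authors mean alternatives, they say so. The severe and critical definitions state that any one criterion is enough, and two inclusion items (symptoms, blood counts) use an and/or internally. Nothing of the kind joins the items to each other.
- The discharge criteria use the same semicolon layout and are evidently cumulative.

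The plain reading is that all items apply.

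**Step 2. Test the imaging item against each class on admission.**

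| Class (Section 2.2) | What the definition says about pneumonia on imaging | Can the imaging item be met? |
|---|---|---|
| Mild | Absent by definition | No |
| Moderate | Present by definition | Yes |
| Severe | Not excluded | Yes |
| Critical | Not excluded | Yes |

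One of four classes is empty at baseline. A patient who develops pneumonia later could meet the item then, but would no longer be mild.

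**Step 3. Carry this into the outcome.**
- On the four-class scale there are 4 × 3 = 12 possible changes from one class to another. The 3 that start at mild (to moderate, severe or critical) cannot be observed.
- The stated target covers 2 × 2 = 4 paths: from mild or moderate, to severe or critical. The 2 that start at mild are lost.
- On the three-class scale of Section 2.3 there are 3 × 2 = 6 possible changes, and none disappears in name. The combined lower class is still populated, but by moderate cases only.
- A patient could still reach mild after treatment, once imaging clears. The gap is at baseline.

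**Step 4. Neighbouring items that the same edit touches.**
- *Laboratory item.* It joins nucleic acid and antibody positivity with an and. No other passage says otherwise, so this is unclear and not contradictory.
- *Consent.* Section 2.2 asks for "ability to provide a signed informed consent form". Section 2.8 says "Study patients or their authorized surrogates received sufficient explanation and time to sign the informed consent form". The two can be read together if a form signed by a surrogate counts, but Section 2.2 does not say so.
- *Discharge.* One criterion in Section 2.2 calls for resolution of infiltrates on lung imaging. A mild patient has none, so that criterion also presumes that mild cases are absent.

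**The case against.** The strongest defence is that the list is a condensed diagnostic work-up. The sentence before it ties eligibility to a national programme that is not shown here, and that programme may combine history, symptoms, blood counts, imaging and laboratory results in some other way. The article condenses a fuller protocol, and its aims and procedures speak of mild patients as enrolled. This stands in part: it makes it plausible that the authors never meant to exclude mild cases. It does not rescue the wording, because the items are presented as the study's inclusion criteria together with age and consent, and no passage makes imaging optional.

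It is also fair to say that mild is not analysed as a class of its own by name. Section 2.3 pools it with moderate, and Section 2.4 does not mention it. That limits the consequence to the content of the pooled group and to the four-class label.

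Stronger readings are tempting, and the documents do not support them:
- *That the consent passages contradict each other.* Section 2.2 does not say that the patient personally must sign, and Section 2.8 can be taken as specifying who may.
- *That the laboratory item drops a sizeable share of early cases.* It conflicts with no other passage, and the article gives nothing on antibody timing from which a share could be derived.
- *That severity mix will vary between sites.* Section 2.2 names one admitting hospital.

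**Conclusion.** The imaging item and the mild definition in Section 2.2 are incompatible as written. No patient who is mild on admission can meet the list, so one of four classes is empty at baseline and the combined mild-and-moderate group is moderate only. Progression from mild disease, which is part of the stated aim, cannot be studied in patients who begin there.

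The conclusion rests on one assumption, that the inclusion items are cumulative. This is the plain reading but is not stated outright. If the authors meant the items as alternatives, the defect is one of wording and still needs correcting. The number of patients affected cannot be estimated, because the article gives no expected distribution by class.

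The laboratory and consent items are secondary clarifications, not proven contradictions. The point should be corrected: a stated rule defeats part of the study's purpose, and the remedy is cheap.

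**What to change.** In Section 2.2:
1. Make the imaging item non-mandatory. Either record imaging features as baseline data, which Section 2.5 already collects, or require the item only for classes other than mild.
2. State that eligibility rests on the confirmed COVID-19 diagnosis already named in the section's first sentence, and that all four severity classes may enrol.
3. State whether nucleic acid and antibody positivity are both required or whether either is enough.
4. Add to the consent item that the form may be signed by the patient or an authorized surrogate, in line with Section 2.8.
5. Reconcile the discharge criterion on infiltrates with the mild class. How it should read is a clinical decision for the investigators.

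The history, symptom and blood-count items need not be dropped to cure the defect.

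The cost is protocol wording and an ethics notification, with no added procedure. The downside is a somewhat milder case mix.
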